**Correspondence:**

**List of Abbreviations**

| CONSORT | Consolidated Standards of Reporting Trials |
| --- | --- |
| OEA | Open elbow arthrolysis |
| MEPS | Mayo Elbow Performance Score |
| SF-36 | Short Form 36-item Health Survey |

**Protocol Summary**

| **Short Title** | Postoperative Elbow rehabilitation |
| --- | --- |
| **Objectives** | This study aims to assess the efficacy of WeChat–based plus scene–graphics health education following open elbow arthrolysis. |
| **Study Design** | This study is a single-center, interventional, historical control study. |
| **Ethical Registration Number** | 2020–028 |
| **Clinical Research Registration Number** | ChiCTR2000036004 |
| **Study Center** | Shanghai sixth people’s hospital, China Shanghai |
| **Primary Outcome** | The primary outcome was the difference in elbow range of motion after 1-week, 6-weeks and 12-weeks post-operative. |
| **Secondary Outcome** | 1-week, 6-weeks and 12-weeks of Psysiological function in quality-of-life scores(SF-36), elbow function by using Mayo Elbow Performance Score(MEPS), assessing the incidence of complications through clinic manifestations and examination results. |
| **Population** | 112 patients diagnosed as elbow stiffness that need to undergo open elbow arthrolysis will be recruited and enrolled into the WeChat group (n=56) or the Control group (n=56). |
| **Study Duration** | 15 months |
| **Follow-up visit** | 1-week, 6-weeks and 12-weeks post-operative |
| **Intervention Group** | Received health education using WeChat and scene–graphics. The information in 4-part comics was shared via a WeChat public account. The patients got information from the account and had daily lessons during hospitalization, and online instruction in a WeChat group after discharge until 12 weeks post-operation. |
| **Control Group** | traditional health education  Received the usual health education provided by the hospital, which includes verbal instructions and electronic materials. Patients in this group did not receive any WeChat-based or scene-graphics education. |
| **Main Inclusion Criteria** | 1. Patients must be aged >18 years old.  2. Must have a diagnosis of elbow stiffness requiring surgical intervention.  3. Must be willing and able to provide informed consent.  4. Must be able to understand and communicate in Mandarin, as the WeChat public account and group will be conducted in these languages.  5. Must have access to a smartphone with WeChat application installed for the intervention group participants. |
| **Main Exclusion Criteria** | 1. Patients with a history of psychiatric disorders or cognitive impairments that would interfere with the ability to comply with the study protocol.  2. Patients who have undergone previous elbow surgeries or have other medical conditions that could affect elbow function.  3. Pregnant women or those planning to become pregnant during the study period.  4. Individuals with known allergies to any of the medications or materials used during the surgical procedure.  5. Patients who are participating in other clinical trials simultaneously or have done so within the past 6 months. |
| **Allocation** | Eligible patients were split into two groups by admission time: the control group (56 patients enrolled from Jan.–Jun. 2021) and the WeChat group (56 patients enrolled from Jul.–Dec. 2021). |
| **Statistical Methodology** | The statistical analysis was conducted using SPSS software version 26.0. The primary outcome measures were elbow range of motion (ROM), which were assessed at baseline, at discharge, and at 1, 6, and 12 weeks post-operation. Secondary outcomes included quality of life, elbow function, and postoperative complications. The data was analyzed using descriptive statistics to summarize the demographic and clinical characteristics of the participants. Inferential statistics, including t-tests for continuous variables and chi-square tests for categorical variables, were used to compare the differences between the control and WeChat groups. Repeated measures analysis of variance (ANOVA) was conducted to evaluate the changes in ROM over time within each group and between the groups. The significance level was set at p<0.05 for all statistical tests. |
| **Safety** | Adverse events will be summarized for each group. The safety analysis will focus on the frequency and severity of any complications that arise during the study period. This includes, but is not limited to, infections, allergic reactions, and any other unexpected medical events that may occur. The safety data will be analyzed to determine if there is a significant difference in the incidence of adverse events between the control and WeChat groups. The results will be reported in accordance with the CONSORT guidelines for randomized controlled trials, ensuring transparency and completeness of the safety data. |
| **Result** | Elbow flexion angle: WeChat group 71.5 (SD 4.2) to 124.2 (SD 11.7) °; Control group 71.7 (SD 4.6) to 114.4 (SD 13.6) ° (diff 10 °, 95% CI 4.9–15.1, P <.001). Elbow extension angle : WeChat group 29.6 (SD 6.0) to 6.4 (SD 2.5) °; Control group 28.8 (SD 3.8) to 10.1 (SD 3.4) ° (diff -4.5 °, 95% CI -6.5– -2.5, P <.001). Forearm pronation angle: WeChat group 31.9 (SD 4.0) to 66.9 (SD 7.3) °; Control group 33.0 (SD 4.2) to 63.1 (SD 7.2) ° (diff 4.9 °, 95% CI 2.0 –7.8, P =.001). Forearm supination angle: WeChat group 30.2 (SD 3.7) to 71.8 (SD 4.8) °; Control group 30.4 (SD 4.1) to 64.2 (SD 9.8) ° (diff 7.7 °, 95% CI 4.4–11.0, P <.001). MEPI score: WeChat group 58.0 (SD 3.7) to 80.4 (SD 5.7); Control group 58.9 (SD 2.8) to 75.8 (SD 6.9) (diff 5.5 points, 95% CI 2.8–8.2, P <.001). SF - 36 score: WeChat group 44.4 (SD 6.6) to 82.0 (SD 7.1); Control group 44.0 (SD 6.4) to 75.0 (SD 11.2) (diff 6.6 points, 95% CI 2.6–10.6, P =.002). |

Content

[List of Abbreviations 1](#_Toc5648)

[Protocol Summary 1](#_Toc8973)

[1. Introduction and Rationale 5](#_Toc6776)

[1.1 Introduction 5](#_Toc12802)

[1.2 Rationale 8](#_Toc10032)

[2. Study Design and Purpose 10](#_Toc13487)

[2.1 Study Design 10](#_Toc9164)

[2.2 Study Purpose 10](#_Toc13211)

[3. Study Population 11](#_Toc16618)

[3.1 Enrollment Population 11](#_Toc9790)

[3.2 Inclusion and exclusion criteria. 11](#_Toc17452)

[3.3 Informed Consent 14](#_Toc24464)

[3.4 Early Withdrawal of subjects 15](#_Toc20744)

[3.5 Replacement of participant 15](#_Toc2086)

[3.6 Early termination of the study 15](#_Toc31974)

[3.7 Interim analyses 16](#_Toc23113)

[4.Study Procedures 16](#_Toc12649)

[4.1Participant recruitment 17](#_Toc14242)

[4.2 Blinding 17](#_Toc13786)

[4.3 Intervention 17](#_Toc11637)

[4.4 Study Duration 25](#_Toc16652)

[5.Data 29](#_Toc25472)

[5.1 Data Collection 29](#_Toc16174)

[5.2 Data Transmission 29](#_Toc4851)

[5.4 Data Storage 30](#_Toc4970)

[5.5 Data Sharing 30](#_Toc20005)

[5.6 Cancellation of Participation 30](#_Toc6979)

[5.7 Researcher Confidentiality 31](#_Toc26350)

[5.8 Data Retention Period 31](#_Toc10761)

[6. Safety 31](#_Toc28880)

[6.1 Related to the surgical site 31](#_Toc9447)

[6.3Abnormal rehabilitation progress 33](#_Toc1357)

[6.2 Safety of Data Collection 34](#_Toc27726)

[7. Study Monitoring 36](#_Toc25635)

[7.2 Collect patient's feedback 36](#_Toc26060)

[8. Ethical Considerations 36](#_Toc5706)

[Appendix 1. 38](#_Toc20883)

[Informed Consent 38](#_Toc12767)

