**3. Study Population**

**3.1 Enrollment Population**

The enrollment population consisted of patients who met the inclusion criteria, which included individuals with elbow stiffness or limited range of motion following elbow trauma or surgery. Exclusion criteria were applied to ensure the safety and validity of the study, such as patients with severe medical conditions that could interfere with rehabilitation or those who were unable to comply with the study protocol. The demographic characteristics of the enrolled patients, including age, gender, and the nature of their elbow conditions, were recorded to ensure a balanced comparison between the WeChat group and the control group. The study's recruitment process was designed to be inclusive yet rigorous, aiming to gather a diverse yet comparable sample for the analysis of the educational intervention's impact on rehabilitation outcomes.

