**4.4.3 Statistical Method**

SPSS Statistics version 26.0 (IBM Corp) was utilized for the data analysis. The chi-square test was used to analyze sex, disease side, and the incidence of postoperative complications. The collected data were subjected to a comprehensive statistical analysis to evaluate the effectiveness of the intervention on elbow stiffness. The normality of the data was first assessed using the Shapiro-Wilk test. For variables that satisfied the normality test, parametric statistical methods were employed, including the paired sample t-test for comparing pre-intervention and post-intervention values. For variables that did not meet the normality assumption, non-parametric tests, specifically the Wilcoxon signed-rank test, were utilized. The changes in elbow range of motion (ROM), the Mayo Elbow Performance Score (MEPS), and the Short Form-36 (SF-36) health survey scores at each time point were analyzed using repeated measures analyses of variance (ANOVA). The results were presented as mean ± standard deviation (SD) for continuous variables and as frequencies and percentages for categorical variables. In cases where the data were not normally distributed, median values and interquartile ranges (IQRs) were reported. The level of statistical significance was set at a two-tailed P value < .05. All statistical analyses were performed using appropriate software to ensure accuracy and to provide a robust interpretation of the study findings.

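### Group coincides with calendar half-year, yet the protocol names no adjustment, commits to the reporting guideline for randomised trials and claims efficacy without a design caveat

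*Protocol*

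**What the plan says.** The Protocol Summary gives the design as: "This study is a single-center, interventional, historical control study". Sections 1.2 and 2.1 repeat the historical control label. The Allocation row says "Eligible patients were split into two groups by admission time" and gives the periods as "the control group (56 patients enrolled from Jan.–Jun. 2021) and the WeChat group (56 patients enrolled from Jul.–Dec. 2021").

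For comparing groups, the Statistical Methodology row names "t-tests for continuous variables and chi-square tests for categorical variables, were used to compare the differences between the control and WeChat groups", plus repeated measures ANOVA. Section 4.4.3 says of ROM, MEPS and SF-36 that the changes "at each time point were analyzed using repeated measures analyses of variance (ANOVA"), and adds: "The chi-square test was used to analyze sex, disease side, and the incidence of postoperative complications". Neither place mentions covariates, matching, weighting or a period term.

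Section 3.1 says that age, gender and the nature of the elbow condition "were recorded to ensure a balanced comparison between the WeChat group and the control group".

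The Safety row states: "The results will be reported in accordance with the CONSORT guidelines for randomized controlled trials". The Objectives row sets out to assess efficacy, and the Result row prints differences, confidence intervals and P values with no remark on the design.

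**The concern.** The two cohorts do not overlap in time. Anything that changed between the first and second half of 2021 (team experience, ward routine, referral pattern, season) enters the group difference in full, and the confidence intervals make no allowance for it. Recording patient characteristics describes imbalance but does not remove it, so section 3.1 promises more than its method delivers. Chi-square tests of sex and side likewise leave the effect estimate unadjusted.

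The guideline for randomised trials contradicts the stated design. Together with efficacy wording and bare P values, it invites a causal reading that consecutive cohorts cannot support. Every primary and secondary comparison is affected.

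**Working it through.** **Inputs.** Protocol Summary, Allocation row: 56 patients per group, in adjacent half-years. Result row: baseline and final means and SDs, differences and 95% CIs.

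**Step 1: reproduce the stated effects.** Difference in change = (final − baseline) WeChat − (final − baseline) control.
- Flexion: (124.2 − 71.5) − (114.4 − 71.7) = 52.7 − 42.7 = 10.0 (stated 10)
- Extension: (6.4 − 29.6) − (10.1 − 28.8) = −23.2 + 18.7 = −4.5 (stated −4.5)
- Pronation: (66.9 − 31.9) − (63.1 − 33.0) = 35.0 − 30.1 = 4.9 (stated 4.9)
- Supination: (71.8 − 30.2) − (64.2 − 30.4) = 41.6 − 33.8 = 7.8 (stated 7.7, rounding)

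MEPS (5.5) and SF-36 (6.6) reproduce in the same way. Plain final-value differences (9.8, −3.7, 3.8 and 7.6 for the angles) do not fit.

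For the CIs, the SD of change is built from the stated SDs with an assumed baseline–final correlation r, using t on 110 df. For flexion at r = 0, SE = √[(4.2² + 11.7² + 4.6² + 13.6²)/56] = 2.54, giving 4.97 to 15.03 (stated 4.9 to 15.1). For extension at r = 0.2 the result is −6.5 to −2.5, as stated. All six intervals agree to about 0.2 with r between 0 and 0.2. The printed effects are thus unadjusted differences in change.

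**Step 2: baseline comparability.** Flexion differs by −0.2 (95% CI −1.9 to 1.5) and pronation by −1.1 (−2.6 to 0.4). All six baseline intervals include zero. Adjusting only for the outcome's own baseline, with a slope assumed anywhere from 0 to 1, gives flexion 9.8 to 10.0, extension −3.7 to −4.5, pronation 3.8 to 4.9 and supination 7.6 to 7.8.

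**Step 3: shift that brings the CI to zero.** This is the stated CI limit nearer zero, divided by the stated effect for the percentage.

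**Step 4: cost of a linear admission-date term.** Assume even accrual over 12 months, with admission time T uniform on 0–12 and group G stepping at month 6. Then Var(T) = 12, Var(G) = 0.25 and Cov(T, G) = 0.5 × 9 − 6 × 0.5 = 1.5. The correlation is 1.5/√(12 × 0.25) = 0.866, and the variance inflation is 1/(1 − 0.75) = 4. The SE doubles. The last column doubles each stated half-width with the point estimate held. It shows lost precision and does not predict the adjusted result.

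| Outcome | Stated effect (95% CI) | Shift to zero (% of effect) | CI with doubled SE |
|---|---|---|---|
| Flexion | 10 (4.9 to 15.1) | 4.9 (49%) | −0.2 to 20.2 |
| Extension | −4.5 (−6.5 to −2.5) | 2.5 (56%) | −8.5 to −0.5 |
| Pronation | 4.9 (2.0 to 7.8) | 2.0 (41%) | −0.9 to 10.7 |
| Supination | 7.7 (4.4 to 11.0) | 4.4 (57%) | 1.1 to 14.3 |

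**Step 5: error rate under a pure period shift.** The flexion CI implies an SE of 5.1/1.98 = 2.57 and an SD of change of 2.57 × √28 = 13.6. Suppose the intervention does nothing and the second half-year is better by 0.1, 0.2, 0.3 or 0.5 SD of change (flexion 1.4, 2.7, 4.1 or 6.8 degrees; assumed sizes). The chance of a significant result favouring WeChat is then about 8%, 18%, 36% or 75%, against a nominal 2.5%.

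**Step 6: can the control half-year reveal drift?** With 56 patients spread evenly over 6 months, the SD of admission time is 6/√12 = 1.73 months. The slope SE is 13.6/(1.73 × √56) = 1.05 degrees per month, so the CI is about ±2.1. A steady drift of 4.9/6 = 0.8 degrees per month, enough to bring the flexion CI to zero, would usually go undetected.

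**The case against.** The protocol is open about its design. It says historical control in several places and never claims randomisation to group; the only random assignment, in section 4.1, is of patients to nurses. The guideline for randomised trials is cited in one sentence about safety data. A reader might infer that the study is being presented as a randomised trial, but the document does not support that. What stands is the conflict between the cited guideline and the stated design.

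A reader might also infer that case-mix differences have been shown to drive the result. They have not. The baseline outcome means are close, the effects are already differences in change, and baseline adjustment alone reverses no direction. Case mix remains open only through prognostic factors that are not shown.

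Section 4.2 gives a reason for allocating by time (limiting contact between groups) and describes standardised measurement with calibrated instruments. The periods are adjacent and at one centre. These points make large drift less likely but do not exclude it.

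Covariates could be listed in a separate SAP. However, the protocol itself names its methods and prints results, and those results are unadjusted.

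Finally, regression cannot cure the design. This is correct: a change in care at July is the same variable as group. A linear date term handles only smooth drift and, as steps 4 and 6 show, does so imprecisely.

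**Conclusion.** The concern holds in this form. Consecutive, non-overlapping cohorts are compared with no named adjustment, the reporting guideline contradicts the design, and efficacy is claimed without a caveat. The documents do not show that the effect is spurious, nor which way any bias runs.

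A shift of 41–57% of the stated effect would bring the interval for any of the four angles to zero; this follows from the printed intervals alone. With a linear date term, even accrual and point estimates held, flexion and pronation would include zero while extension and supination would still exclude it. It would therefore be wrong to say that the whole primary outcome loses significance under trend adjustment. The error rates in step 5 rest on assumed shift sizes and show sensitivity only.

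**What to change.** 1. Make the main between-group analysis a regression (ANCOVA or a mixed model) adjusted for data already recorded: baseline value, age, sex, side and nature of the elbow condition. Reword section 3.1 so that recording these is not said to ensure balance.
2. Report an admission-date trend analysis as a sensitivity analysis only. State that it assumes linear drift, cannot remove a step change at July and is imprecise.
3. Replace the guideline for randomised trials in the Safety row with one for non-randomised intervention studies.
4. Word the conclusion as an association between consecutive cohorts, and state that period effects cannot be separated from the intervention.

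The cost is analysis code and wording, with no new data. The price is wider intervals in the sensitivity analysis and a more modest conclusion.

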**2. Study Design and Purpose**

**2.1 Study Design**

The study was designed as a historical control study to assess the effectiveness of a WeChat-based health education program that incorporates scene-graphics in the rehabilitation process following open elbow arthrolysis.

The study was conducted over a period of 15months, with a total of 112 patients who underwent open elbow arthrolysis being enrolled. The patients were divided into two groups: the WeChat group, which received the WeChat-based plus scene-graphics health education, and the control group, which received traditional educational intervention. The primary outcome measure was the improvement in elbow range of motion (ROM) at the end of the 1-week, 6-weeks, 12-weeks post-operative period. Secondary outcomes included , the quality of life , elbow function and the rate of complications. Data were collected at baseline, at 1-week, 6-weeks, and 12-weeks postoperatively. The study aimed to determine whether the innovative educational approach could enhance patient recovery and engagement in rehabilitation, leading to better clinical outcomes.

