**2.2 Study Purpose**

**2.2.1Primary purpose**

The primary objective of this study was to evaluate the effectiveness of a novel WeChat-based health education program that integrates scene-graphics in the rehabilitation process of patients undergoing open elbow arthrolysis. By comparing the outcomes of patients in the WeChat group with those in the control group, the study sought to ascertain if the innovative approach could lead to significant improvements in elbow range of motion, quality of life, and function, as well as a reduction in the rate of complications.

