**4.2 Blinding**

No blinding was implemented in this study. The surgical team and research members were aware of group allocations, as the intervention required explicit instructions for the WeChat-based rehabilitation program. Patients were enrolled into different groups at varying admission times to minimize interaction, and all participants were informed about the study procedures without masking group details. Primary outcomes (e.g., elbow range of motion, MEPS scores) were measured using standardized protocols with calibrated instruments, minimizing subjective bias. All data were recorded electronically and analyzed by a statistician unaware of group allocations.

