**4.4.1.1Primary Outcome**

The elbow range of motion (ROM) was measured by using a handheld goniometer and consisted of four angles: elbow flexion and extension, forearm pronation, and supination [41, 42]. The ROM was measured three times by a surgeon using three landmarks (the lateral epicondyle, the tip of the acromion process, and the middle portion of the wrist)., after which the average ROM was calculated.

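### The primary outcome is four angles at three visits, all tested at 0.05 with no key visit, success rule or adjustment, and MEPS is called both primary and secondary

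*Protocol*

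**What the plan says.** - **Primary outcome and visits.** The Protocol Summary states: "The primary outcome was the difference in elbow range of motion after 1-week, 6-weeks and 12-weeks post-operative". Section 2.1 names the same three visits: "The primary outcome measure was the improvement in elbow range of motion (ROM) at the end of the 1-week, 6-weeks, 12-weeks post-operative period". Neither singles one out.
- **Components.** Section 4.4.1.1 says that range of motion "consisted of four angles: elbow flexion and extension, forearm pronation, and supination". No total arc, composite or leading angle is defined.
- **Significance level.** The Summary says "The significance level was set at p<0.05 for all statistical tests". Section 4.4.3 adds that the level is two-sided: "The level of statistical significance was set at a two-tailed P value < .05".
- **Tests.** The Summary's Statistical Methodology row offers between-group t-tests for continuous variables and also repeated measures ANOVA for range of motion. Section 4.4.3 describes paired pre/post t-tests and repeated measures ANOVA. Neither place says which analysis decides the primary outcome.
- **Status of MEPS.** Section 4.2 reads "Primary outcomes (e.g., elbow range of motion, MEPS scores) were measured using standardized protocols". The Summary and section 4.4.1.2 place elbow function, measured by MEPS, among the secondary outcomes.
- **Results.** The Result row of the Summary gives baseline and one follow-up mean for each angle, MEPS and SF-36, with a difference, 95% CI and P value. It does not say which visit the follow-up is.

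**The concern.** Four angles at three visits make up to 12 primary comparisons, each at 0.05. With no statement of what counts as success, a significant result on any one of them could be presented as a positive primary finding. The nominal 5% would then not describe the risk of a false primary claim. The unlabelled visit in the Result row adds to this, because a reader cannot tell which of the primary comparisons is shown or whether that visit was fixed in advance. The double status of MEPS leaves the size of the primary family itself uncertain.

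This is more than detail left to an analysis plan. The protocol states 0.05 for every test as a rule, so an analysis plan that adjusted would depart from the protocol. The conflict over MEPS lies within the protocol text.

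**Working it through.** The protocol states no family-wise error rate, power or sample-size derivation, so there is no design figure to reproduce. Its only error figure is 0.05 two-sided per test.

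**1. Independent tests.** Chance of at least one false positive among k tests = 1 − 0.95^k.

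| Reading | k | Chance | 0.05/k |
|---|---|---|---|
| One test per angle | 4 | 1 − 0.95^4 = 18.5% | 0.0125 |
| One test per angle, plus MEPS | 5 | 22.6% | 0.0100 |
| Four angles × three visits | 12 | 1 − 0.95^12 = 46.0% | 0.0042 |
| The same, plus MEPS at three visits | 15 | 1 − 0.95^15 = 53.7% | 0.0033 |

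The Statistical Methodology row also says of range of motion "which were assessed at baseline, at discharge, and at 1, 6, and 12 weeks post-operation". Counting discharge would give 16 angle tests and 56.0%, but the definitions of the primary outcome do not include that visit.

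**2. Correlated tests.** The protocol gives no correlations, so these are assumed: 0 to 0.7 between outcomes and 0.3 to 0.9 between visits. The simulation used multivariate normal test statistics, 200,000 draws per setting and a two-sided 0.05 for each test.

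| k | Lowest (correlations 0.7 / 0.9) | Highest correlated case (0 / 0.3) | Independent |
|---|---|---|---|
| 12 | 20.6% | 44.2% | 46.0% |
| 15 | 23.3% | 51.8% | 53.7% |

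For four tests at one visit the range is 13.2% (correlation 0.7) to 18.5% (correlation 0). For five tests it is 14.8% to 22.7%.

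**3. What the printed differences are.** Change in the WeChat group minus change in the control group, from the Result row:

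- Flexion: (124.2 − 71.5) − (114.4 − 71.7) = 52.7 − 42.7 = 10.0; printed 10. The follow-up means differ by 9.8.
- Extension: (6.4 − 29.6) − (10.1 − 28.8) = −23.2 + 18.7 = −4.5; printed −4.5. The follow-up means differ by −3.7.
- Pronation: (66.9 − 31.9) − (63.1 − 33.0) = 35.0 − 30.1 = 4.9; printed 4.9. The follow-up means differ by 3.8.
- Supination: (71.8 − 30.2) − (64.2 − 30.4) = 41.6 − 33.8 = 7.8; printed 7.7, which rounding can explain. The follow-up means differ by 7.6.

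So the printed contrast is a between-group difference in change from baseline. The statistical text does not name that contrast as decisive.

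**4. Do the printed results survive adjustment?** SE = (CI width / 2) / t(0.975; 110 df), and t = difference / SE.

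| Outcome | SE | t | P |
|---|---|---|---|
| Flexion | 2.573 | 3.89 | 0.0002 |
| Extension | 1.009 | −4.46 | 0.00002 |
| Pronation | 1.463 | 3.35 | 0.0011 |
| Supination | 1.665 | 4.62 | 0.00001 |
| MEPS | 1.362 | 4.04 | 0.0001 |

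These agree with the printed P values. The Holm thresholds for four angles, from smallest to largest P, are 0.0125, 0.0167, 0.025 and 0.05. All four angles are below the strictest of these, and all four and MEPS are below 0.05/15 = 0.0033.

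**The case against.** - **Twelve tests is only one reading.** Repeated measures ANOVA can mean one overall test per angle, which gives four tests and 13–19%. This stands, and it is why a range is given. Even the low end is more than twice 5%.
- **Inflation needs an any-one-wins rule.** The protocol states no success rule. If every angle at every visit had to be significant, the error would be at most 5% without adjustment. This stands as a condition on the figures. The defect is that success is left undefined while 0.05 is fixed for every test.
- **All four angles are reported and all are strong.** This stands. No angle was left out of the Result row, and the P values survive Bonferroni for 15 tests. A reader might infer that the printed findings are false positives from multiple testing, and the figures do not support that. Nor do they say anything about bias from a historical control or from the absence of blinding.
- **The primary objective is broad.** A reader might infer from section 2.2.1, which asks whether the programme could "lead to significant improvements in elbow range of motion, quality of life, and function, as well as a reduction in the rate of complications", that all of these are primary outcomes. An objective is not a list of primary endpoints, and the Summary and sections 2.1 and 4.4.1.2 consistently list quality of life, function and complications as secondary. The contradiction is confined to MEPS in section 4.2, where it appears as an example in the blinding paragraph.
- **A protocol need not report results.** This is correct. Results for the other visits or for complications that are absent from a summary row are a reporting matter. Only the missing time-point label bears on this point.

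**Conclusion.** The point holds in a limited form. The protocol defines a primary family of four angles at three visits, fixes 0.05 for every test, gives no key visit, key angle, success rule or adjustment, and contradicts itself on MEPS. If one significant test is enough for a positive primary claim, the family-wise error is about 13–19% with one test per angle, about 21–46% with 12 tests, and up to 54% with MEPS included. The ranges rest on assumed correlations, and the upper ends assume independence.

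A reader might go further and call a false-positive primary result likely. The figures do not support that: the 12 angle tests give at most 46%, and 50% is passed only by adding MEPS or the discharge visit under independence or weak correlation. The practical effect on the printed angle results appears small, since they pass adjustment. Whether that settles the matter for a 12-week primary analysis depends on their being the 12-week values, which the Result row does not say.

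**What to change.** 1. Name 12 weeks as the primary time point. It is the last follow-up visit and the end of the education programme in the Summary.
2. Name one decisive between-group analysis. The difference in change from baseline matches what is printed.
3. Test the four angles at 12 weeks with Holm at an overall two-sided 5%, and limit the statement on 0.05 for all tests accordingly.
4. Treat the 1- and 6-week angles, MEPS, SF-36 and complications as secondary.
5. Correct section 4.2 so that MEPS is not listed as primary.
6. Label the follow-up time point in the Result row.
7. State that this hierarchy was set after results were known. It makes the claim transparent but cannot restore prespecified error control.

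The cost is wording and one Holm step, and the 1- and 6-week results lose primary status. If the printed values are the 12-week ones, no angle would lose significance. If they are not, that cannot be said until the 12-week values are shown.
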